#### Intervention

The intervention has 10 child sessions and 2 sessions for the parents. To strengthen the effectiveness of our intervention, it is based on a theoretical framework including both risk and protective factors (as recommended by Cuijpers [24]).The following themes are addressed: family functioning and social network, being proud of strengths, focus on positive emotions and events, problem solving, and breaking the cycle of avoidance behaviour. The latter will either be focussed on behavioural activation (indication for depressive symptoms [35]) or on exposure exercises (indication for anxiety symptoms). The therapist addresses each of the themes in the first sessions and then elaborates on the most appropriate module(s) for each child. In collaboration with the child and the parents, the child chooses 10 steps to work on throughout the sessions. These steps are in line with the aforementioned themes, and could encompass engaging in specific activities, exposure exercises, and exercises on strengths and resilience. Throughout the sessions, the child regularly monitors the frequency and type of activities (categorised as either alone or with others, and either at home or elsewhere). Ideally, children should have satisfying activities in each of these four categories. This registration is available for mediation analyses. The first session is with the parents only. The therapist makes a plan with the parents on how to give age-appropriate information on the parental anxiety or mood disorder to the child in the next session. Parents also receive information on the possible effect on offspring and protective factors against future child psychopathology (such as having a parent or key figure they can trust, and openness in the family). Two more parent sessions further elaborate on positive parenting and defining the social network in terms of social support for the family.

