**Method/design:**

The current STERK-study (Screening and Training: Enhancing Resilience in Kids) is a randomized controlled clinical trial combining selected and indicated prevention: it is targeted at both high risk individuals without symptoms and at those with subsyndromal symptoms. Individuals without symptoms meet two of three criteria of the High Risk Index (HRI; female gender, both parents affected, history of a parental suicide (attempt). This index was developed in an earlier study and corresponds with elevated risk in offspring of depressed patients. Children aged 8–17 years (n = 204) with subthreshold symptoms or meeting the criteria on the HRI are randomised to one of two treatment conditions, namely (a) 10 weekly individual child CBT sessions and 2 parent sessions or (b) minimal information. Assessments are held at pre-test, post-test and at 12 and 24 months follow-up. Primary outcome is the time to onset of a mood or anxiety disorder in the offspring. Secondary outcome measures include number of days with depression or anxiety, child and parent symptom levels, quality of life, and cost-effectiveness. Based on models of aetiology of mood and anxiety disorders as well as mechanisms of change during interventions, we selected potential mediators and moderators of treatment outcome, namely coping, parent–child interaction, self-associations, optimism/pessimism, temperament, and emotion processing.

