To date, preventive interventions have been designed to prevent either mood disorders or anxiety disorders. Keeping in mind the significant overlap in symptoms between depression and anxiety disorders, prevention studies should focus on both. Indeed, epidemiological studies have found that elevated symptoms of anxiety and depression occur in offspring of both anxious [30] and depressed patients [31]. Since the aetiology and pathogenesis of anxiety and depression also have considerable overlap, including offspring from patients with both mood and anxiety disorders provides the opportunity to study common mediating factors.

From a societal point of view, it is important to study the economic impact of psychiatric illnesses and possible effects of prevention programs, to assist future policy making and resource allocation. The economic evaluation in our study will focus on the differential effects on short and long term costs and health outcomes of the treatment conditions under study: CBT or minimal information. The study will be conducted from a societal perspective [32].

Treatment outcome studies typically include variables to study the treatment mechanisms (“how does the treatment work”) as well as the moderators of treatment outcome (“for what groups does the treatment work”)[33]. With regard to mediating factors in the current study, the intervention will aim at changing coping behaviour [34], increasing activities [35], and enhancing trust in the availability of attachment figures (in the social network). Even though we do not address cognitions directly through cognitive restructuring, we nonetheless want to investigate if the child’s attributional style changed through our behaviour intervention.

Moderating factors associated with (non)response are current parental psychopathology [14] and child’s symptomatology (internalising and externalising). We additionally measured some stable child characteristics that have been associated with the onset of anxiety or mood disorders, but have not been studied in relation to treatment outcome in offspring, namely reactive and regulative temperament [36], general executive functioning, and automatic self-associations [37]. In addition, some of the presumed mediating factors may also function as moderators.

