### Trial objective and purpose

The primary goal is to investigate whether a brief (10 + 2 sessions) cognitive behavioural treatment program on resilience and symptom reduction can prevent the incidence of depression or anxiety disorder in an ultra high risk sample of 8–18 year old offspring of patients with unipolar depression or anxiety disorder (sample defined by a High Risk Index or subclinical symptoms, or both). The second goal is to examine whether this intervention meets current standards for cost-effectiveness. A third goal is to explore the role of a number of factors that may potentially mediate or moderate the effect of the intervention. Mediating factors include coping, attributional style, daily activities, and optimism, while the selected moderating variables are child temperament characteristics and executive functioning, parental psychopathology (of both parents), child symptomatology, attachment, and (automatic) self-associations.

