#### Randomisation

Since outcome may be dependent on treatment centre and the pathway of inclusion (through elevated symptoms versus no symptoms/HRI only), we decided to work with stratified allocation to treatment condition to ensure a balanced number of participants over conditions. A web-based computer program allows for dynamic on-the-spot randomisation. Randomisation is based on the defined strata as well as on the assigned treatment condition of earlier subjects within the strata. To prevent conscious or unconscious influence on the recruiting team, we choose to conceal the exact details of the randomisation process at this stage (following the recommendations of the CONSORT guidelines [39]). Randomisation takes place after the whole assessment has been completed, so that the first assessment is not dependent on the participant’s knowledge of treatment condition. The research assistant assigns a unique code to each participant. In case one family has several high risk children, the youngest child is entered for randomisation, and the siblings are assigned to the same condition. The research assistant then enters the number of the participant in the web-based randomisation program, and at that moment the computer randomly assigns the treatment condition (active intervention or minimal information; 1:1).

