#### Measures

##### Primary outcome

Our primary outcome is the time to onset of depression or anxiety disorders in the offspring, based on the Child version of **Diagnostic Interview Schedule for Children** Version IV NIMH DISC-IV; [40], which is a highly structured diagnostic assessment instrument designed to gather symptom presence for child and adolescent psychiatric disorders based on the symptoms and criteria variables as defined in the Diagnostic and Statistical Manual of Mental Disorders DSM-IV; [41]. The computerized DISC is administered via a computer (the interviewer reads questions from the computer screen and enters responses directly into the computer) and scored by computer algorithm [42]. There are parallel versions of the instrument: the DISC-P for parents, and the DISC-C for direct administration to children. In the present study the DISC-C is used to assess anxiety disorders and depression, and a brief assessment of alcohol and drug use. The DISC-P is used as a parent report of children’s anxiety and depression symptoms as well as questions about whole life symptomatology. At the 12- and 24-follow-up assessments, the interviewer addresses the past 12 months. If any disorder was present, the interviewer makes an estimation of the time of onset and the duration of the disorder. The interviewer combines information retrieved from the DISC with the **Weekly Emotions Diary for Youth (WEDY;** [name] & [name], Weekly Emotions Diary, unpublished manuscript**)** as input. All children included in the intervention trial are asked to keep a weekly diary during the study, giving scores of three items: anxiety, sad mood, and happiness on a 0–5 scale. This chart was developed for the purpose of the current study, primarily as a helpful tool to obtain a good estimate of the onset and duration of a disorder (if present by DISC-criteria), since children may not always have an adequate sense of time when retrospectively reporting over the past year. Children are encouraged to fill out the diaries either on paper or through the internet in a web-based diary. They receive an incentive of 1 euro per month for completing the weekly diary, with a maximum of 25 euros.

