### Sample size calculation

Our sample size calculation is based on the conventional significance (alpha) and power (1-beta) levels of 0.05 and 0.80 respectively, planning one-sided testing. We assume a baseline incidence rate of mood and anxiety disorders of 0.11/person*year for the control condition, based on our own unpublished analyses in high risk offspring from the ARIADNE study; in the ultra-high risk subgroup of children with 2 or 3 risk factors we found a 10-year cumulative incidence of anxiety- and mood-disorders of 0.67 (time frame: age 10–20), which corresponds to an incidence rate of 0.11/person*year, assuming a constant rate. With an intended follow-up duration of 2 years, we would then need a minimum of 81 participants per condition to give our study sufficient power to detect a clinically meaningful effect of the intervention on the time to onset of episodes of mood- and anxiety disorders. We compared our estimated incidence rates with two prevention studies. Clarke et al. [13], who studied the effect of a preventive program in subsyndromal offspring of depressed patients, found a 1 year cumulative incidence of 0.25 for depression alone (rate 0.29/person*year). Therefore, our incidence assumption is relatively conservative. We assume a risk reduction of 70% for the treatment condition, based on the Clarke study; the 1 year cumulative incidence of depression in the intervention group is 0.08, compared to 0.25 in the control group (unadjusted hazard ratio 0.29). The reported adjusted hazard ratio in this study is 0.18. Dadds et al. [67] report a hazard ratio of 0.22 in favor of a program aimed at preventing anxiety disorders in children. Again, we choose the more conservative estimate. Nevertheless, realizing that above-mentioned assumptions remain uncertain and that participants may drop out, we decided to include another 25%, resulting in 2 groups of 102 children for the intervention phase (N = 204).

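### Daily activities is a named mediator, but the only activity data the article describes come from the CBT sessions, so mediation of the randomised effect through activities cannot be estimated as written

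*Protocol article*

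**What the plan says.** The section on trial objective and purpose sets exploration of mediators and moderators as the third goal and states: "Mediating factors include coping, attributional style, daily activities, and optimism". The Background likewise gives an increase in activities as one of the changes the intervention is meant to bring about.

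The Intervention section describes how activities are recorded: "Throughout the sessions, the child regularly monitors the frequency and type of activities". Each activity is classified by company (alone or not) and by place (home or not). The section then says of these data: "This registration is available for mediation analyses".

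The abstract describes the two conditions as 10 weekly child CBT sessions plus 2 parent sessions, or minimal information. The second condition contains no sessions.

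One instrument outside the scheduled assessments does reach both arms: "All children included in the intervention trial are asked to keep a weekly diary during the study". It has three items, scoring anxiety, sadness and happiness.

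**The concern.** To claim that CBT works partly by raising activity, one must first show that allocation changes activity. That requires activity to be measured in both arms, ideally with a value from before randomisation. Here the source named for the mediation analysis belongs to the treatment and exists only where the treatment is given.

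What such data can support is an association, within the CBT arm, between recorded activity and outcome. Children who are less unwell or more engaged may both record more activities and stay well. The therapy also asks each child to choose and carry out steps that can themselves be activities, so the register partly records engagement with treatment. At stake is one component of an exploratory goal. The primary test of time to onset is not affected.

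**Working it through.** **Inputs**

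- Planned size (Sample size calculation): 81 per condition plus 25%. Check: 81 × 1.25 = 101.25, rounded up to 102 per arm, or 204 in total. This agrees with the article.
- Allocation (Randomisation): 1:1, made after the first assessment is complete.
- Mediator source (Intervention): the register kept in the course of the CBT sessions.

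**Step 1. Is there an activity measure for controls anywhere in the article?**

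| Place | What it holds | Activity measure in both arms? |
|---|---|---|
| Table 1 (screening) | HRI and demographics, RCADS, BIS, SNAP, PANAS, LOT/YLOT | No |
| Table 2 (intervention phase) | Includes coping (CSLK), attributions (CASQ) and optimism (YLOT) at T1 to T4 | No |
| Mediator and moderator measures | Child and parent instruments; the closest is the BIS, which rates functional impairment | No |
| Weekly diary (Primary outcome) | Three mood items | No |
| Session register (Intervention) | How often and what kind of activities | CBT arm only |

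Three of the four named mediators therefore have an instrument at four time points in both arms. Daily activities has none.

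**Step 2. Can the effect of allocation on activities be estimated?**

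Let A = 1 for CBT and A = 0 for minimal information, and let M be activity. The first mediation equation is

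M = α + a·A + error,

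and in the usual linear formulation the indirect effect is a × b, where b is the effect of M on outcome given A.

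M is observed only when A = 1. In those 102 rows the column for A equals the intercept column, so the design matrix [1, A] has rank 1 where 2 is needed (confirmed numerically). Only the sum α + a can be estimated. Put differently, a = (mean activity under CBT) − (mean activity under control), and the second term has no data. Any value of a fits the observed data equally well, so a × b is not estimable either.

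**Step 3. Does the planned model rescue it?**

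The Statistical analyses section says mediators can enter the multilevel model as explanatory variables, and it cites that model's handling of missing data. For activities, the missing share would be 102/102 = 100% of controls and 102/204 = 50% of all children, by design. A model can borrow information for values missing from some children in an arm. It has none for a variable never observed in that arm, unless it adds assumptions the data cannot test.

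**Step 4. Is there a baseline?**

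The register belongs to the sessions, which follow randomisation. No pre-randomisation value is described for either arm.

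**The case against.** The strongest objection is that this is a condensed article. It says the register can be used for mediation analyses, not that it is the only source, and Table 2 is not a full inventory: the weekly diary has no row in it. A reader might infer that the trial collects no activity data from controls at all. The article does not support that much, and a fuller protocol could hold such a measure. What remains is that the article itself nominates the session register for this purpose, and that register cannot serve it.

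A second objection is weight. The goal is exploratory, no specific mediation analysis of activities is laid down, and the abstract's list of mediators and moderators omits activities. This stands and limits the importance of the point. The abstract's silence proves little, however, because it also omits attributional style, which is measured throughout. A reader might further infer that the whole mediation goal fails, or that the investigators intend to present a within-arm correlation as a mechanism. The document supports neither.

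Third, the register is not worthless. An early-session entry could serve as a starting value within the CBT arm, and repeated RCADS scores allow partial adjustment for severity. Both are true, but neither supplies a control value.

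Finally, the obvious remedy of adding activity counts to the diary has a real cost. Activity monitoring is described as part of the intervention, so giving it to controls weekly for up to two years could narrow the contrast on the primary outcome. Extra items could also lower completion of a diary that helps date onset. This objection stands, and the fix below avoids that route.

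**Conclusion.** The point holds for one of four named mediators. On the document as written, the effect of allocation on daily activities, and any indirect effect through them, is not estimable, because the mediator is unobserved for all 102 planned control children and has no pre-randomisation value in either arm. This rests on two readings of the article: that minimal information involves no sessions, and that no activity measure exists beyond those described. If a fuller protocol schedules an activity measure in both arms, the point reduces to naming the wrong data source.

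Coping, attributional style and optimism are unaffected, as are the primary outcome, the secondary outcomes and the economic evaluation. The matter is worth correcting because the article pairs a stated goal with a stated data source that cannot support it, and the correction is cheap.

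**What to change.** **Preferred.** Remove daily activities from the mediators of the randomised effect. Describe the session register as process or engagement data for the CBT arm, and report any association with outcome as within-arm and non-causal. This costs only wording.

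**If mediation by activities is to be kept.** Add a brief activity questionnaire in both arms at the existing T1 assessment, completed before randomisation, and at T2. Do not put weekly self-monitoring in the diary. The cost is a few extra items at two visits. According to the Discussion, inclusion was still under way, so children already enrolled would lack the T1 value. The activity analysis would then be restricted to later entrants, and this should be stated. Onsets dated before T2 (month 4) would precede the follow-up mediator value and could not be attributed to it.

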### Assessments

#### Assessment schedule

Baseline assessment takes place at T0 and comprises questionnaires on the child’s and the parent’s wellbeing (see Table 1). This first screening is used to define the high-risk study population. At T4, all children of parents that were willing to participate will be assessed again with the same measures. The latter is important to evaluate the validity of the initial selection of high risk individuals. If a relatively large proportion of the low-risk group nevertheless has developed a mood or anxiety disorder, this would imply that for future prevention programs the selection strategy should be reconsidered. Selection for the intervention phase is based on the HRI and the RCADS (see Figure 1).

**Table 1 T1:** Assessment schedule for screening (T0) and 24 months follow-up screening

**Measures**	**Child**	**Parent 1**	**Parent 2**
Demographics (+ HRI)		X	
Child anxiety and depression (RCADS)	X	X	
Child impairment (BIS)		X	
Child externalizing symptoms (SNAP)		X	
Parent positive and negative affect (PANAS)		X	X
Optimism (LOT/YLOT)	X	X	X

If a child qualifies for “ultra high risk” based on the screening, he or she may enter the intervention phase of the study. The pre-intervention assessment encompasses structured diagnostic interviews with the child and both parents, as well as a number of relevant other measures (see Table 2). Assessments in the intervention phase are planned for month 0 (T1, at the start of the intervention), month 4 (T2), month 12 (T3), and month 24 (T4). A subset of the instruments is also scheduled for month 6 and 18.

**Table 2 T2:** Assessment schedule for intervention phase

**Measures**	**T1**	**T2**	**T3**	**T4**	**Child**	**Parent1**	**Parent2**
Child diagnoses (DISC)	X	-	X	X	X	X	-
Child anxiety and depression (RCADS)	X	X	X	X	X	X	-
Child impairment (BIS)	X	X	X	X	X	-	-
Child externalizing symptoms (SNAP)	X	X	X	X	X	-	-
Child attachment (IPPA)	X	X	X	X	X	-	-
Implicit child attachment (ABT)	X	-	-	-	-	-	-
Child coping (CSLK)	X	X	X	X	X	-	-
Child attributions (CASQ)	X	X	X	X	X	-	-
Child optimism (YLOT)	X	X	X	X	X	-	-
Child self-esteem (RSES)	X	X	X	X	X	-	-
Expressed emotion (FMSS)	X	-	-	-	-	X	X
Implicit Self-associations (EAST)	X	-	-	-	-	-	-
Child executive functions (BRIEF)	X	-	-	-	-	X	-
Child temperament (EATQ)	X	X	X	X	-	X	-
Parent positive and negative affect (PANAS)	X	X	X	X	-	X	X
Parent depression (BDI)	X	X	X	X	-	X	X
Parent anxiety (BAI)	X	X	X	X	-	X	X
Parent substance misuse (AUDIT)	X	X	X	X	-	X	X
Parent optimism (LOT)	X	X	X	X	-	X	X
Parent psychopathology (CIDI)	X	-	-	-	-	X	X
Cost Effectiveness*	X	X	X	X	-	X	X
Quality of life (EQ-5D)*	X	X	X	X	X	X	X

* Cost effectiveness measures and EQ-5D will also be administered at 6 and 18 months.

Note that T1 = pre-intervention, T2 = 4 months follow-up, T3 = 12 months follow-up, and T4 = 24 months follow-up.

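### The 24-month check of the selection strategy is worded as onset of disorder in low-risk children, but they get questionnaires only, so it can speak only to elevated symptoms

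*Protocol article*

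**What the plan says.** The Assessment schedule section describes the screening assessment as questionnaire-based: "Baseline assessment takes place at T0 and comprises questionnaires on the child’s and the parent’s wellbeing (see Table 1"). For the 24-month point it says: "At T4, all children of parents that were willing to participate will be assessed again with the same measures". Table 1 covers both occasions, as its title shows: "Assessment schedule for screening (T0) and 24 months follow-up screening". Its rows are demographics with the High Risk Index (HRI), RCADS, BIS, SNAP, PANAS and LOT/YLOT.

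The purpose of the repeat assessment is given as: "The latter is important to evaluate the validity of the initial selection of high risk individuals". The condition that would prompt a rethink for future programmes is: "If a relatively large proportion of the low-risk group nevertheless has developed a mood or anxiety disorder".

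Diagnostic interviewing begins only once a child has qualified as ultra high risk and enters the intervention phase: "The pre-intervention assessment encompasses structured diagnostic interviews with the child and both parents". The DISC is listed in Table 2 alone, at T1, T3 and T4. The Primary outcome section defines onset of depression or anxiety disorder by the DISC-IV. The interviewer asks about the preceding 12 months at each of the two later visits and uses a weekly diary, kept by children in the intervention trial, to help date onset.

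**The concern.** The check turns on how many low-risk children have become cases, yet the plan gives those children no instrument that identifies a case. The article states both the measures and the inference, so this is a mismatch within the text and not a detail left to a fuller document.

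What is at stake is the conclusion about the selection rule. Combining the HRI with symptoms is presented in the Background as a distinctive feature of the study. If questionnaire results at 24 months were reported under the word disorder, readers would take a proportion with elevated symptoms for an incidence of disorder, and the rule could look better or worse than it is.

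**Working it through.** **Size of the group.** The Sample size calculation section plans 554 screened children, 70% at ultra high risk and 30% not. 554 × 0.30 = 166.2 and 554 × 0.70 = 387.8, which reproduce the stated 166 and 388. I take the low-risk group of the Assessment schedule to be these 166.

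**What each group receives.**

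| Time | Low-risk children | Randomised children |
|---|---|---|
| T0 screening | Table 1 questionnaires | Table 1 questionnaires |
| T1, month 0 | nothing listed | DISC, RCADS and others |
| T2, month 4 | nothing listed | RCADS and others, no DISC |
| T3, month 12 | nothing listed | DISC (past 12 months), RCADS and others |
| T4, month 24 | Table 1 questionnaires | DISC (past 12 months), RCADS and others |
| Weekly diary | no | yes |

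**What the stated condition needs.** To say that a child has developed a disorder, three things are required:
1. A case definition. In this trial it is the DISC, which low-risk children never receive.
2. Knowledge that the child was not a case at the start. Without a diagnostic interview at entry, existing and new disorder cannot be separated.
3. Coverage of the interval. A questionnaire on current symptoms at month 24 does not capture an episode that began and remitted earlier. In randomised children, two DISC interviews each looking back 12 months cover the two years.

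None of the three is met in the low-risk group.

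**Whether the RCADS can stand in for a diagnosis.** It is described as a symptom questionnaire whose scales correspond to disorders. The only cut-off given is the 80th percentile, by age segment, and it defines elevated symptoms for inclusion (Participants section). A child above it is a candidate for prevention. The event to be prevented is the disorder. The article itself keeps the two apart.

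**What can be observed.** Self-report RCADS is collected at T4 in low-risk children (Table 1) and in randomised children (Table 2). The proportion at or above the existing cut-off is therefore available in both groups.

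**Illustration only; the conclusion does not depend on it.** The Background gives cumulative incidence at age 20 of 25% with no risk factor and 45% with one. Assume a constant rate over 10 years, as the article does for its figure of 0.67:
- rate = −ln(1 − 0.25)/10 = 0.0288 and −ln(1 − 0.45)/10 = 0.0598 per year
- two-year incidence = 1 − exp(−2 × rate) = 5.6% and 11.3%
- expected cases = 166 × 0.0559 ≈ 9 and 166 × 0.1127 ≈ 19

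Suppose a positive questionnaire were counted as disorder, with assumed sensitivity 0.60 to 0.95 and assumed specificity 0.80 to 0.90 (neither is in the document). The apparent proportion is sensitivity × incidence + (1 − specificity) × (1 − incidence):
- smallest ratio: 0.60 × 0.113 + 0.10 × 0.887 = 0.156, and 0.156/0.113 ≈ 1.4
- largest ratio: 0.95 × 0.056 + 0.20 × 0.944 = 0.242, and 0.242/0.056 ≈ 4.3

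Missed remitted episodes would push the other way. The illustration shows only that the two quantities are not interchangeable.

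**The case against.** The strongest reply is that this check is peripheral. The Trial objective section names three goals (prevention, cost-effectiveness, mediators and moderators), and validating the selection rule is not among them. It is not a listed outcome, has no threshold or test, and appears as a conditional remark about future programmes. That stands, and it limits the weight of the point.

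A second reply is that the questionnaires are not empty. RCADS scales map onto named disorders, and the parent-rated BIS adds impairment. A large share of low-risk children with raised symptoms and impairment would be a fair reason to look again at the selection. That also stands. A reader might infer that the 24-month screening can say nothing about the selection strategy; the documents do not support that.

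Third, Figure 1 is not shown and might contain a diagnostic step for low-risk children. This cannot be excluded, but the text and the title of Table 1 both point the other way.

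Two further inferences are tempting and should be resisted. One is that the plan would set RCADS results in low-risk children against DISC-based onset in randomised children. No such comparison is proposed; the text speaks only of a proportion within the low-risk group. The other is that a DISC at T4 for low-risk children above the RCADS cut-off would allow the protocol to keep its condition about disorder. It would not. It would miss children whose episode had remitted and who now score low, it would leave much of the first year unobserved because the interview looks back 12 months, and with no entry interview it could not separate new from existing disorder.

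**Conclusion.** The point holds in a limited form. As written, the condition for reconsidering the selection strategy is onset of disorder in a group (planned 166 of 554) that has no diagnostic interview at any time. Onset is not observable in that group. Only a statement about elevated symptoms at 24 months can be made.

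This rests on reading the low-risk group as the 30% not at ultra high risk, and on Figure 1 not adding a diagnostic step. A reader might infer damage to the trial's main result; there is none, because randomised children do receive the DISC, so the primary outcome and the randomised comparison are unaffected. The size given is a planned headcount, not a bias in any estimate. The correction is worth making because it is nearly free and changes what the trial may conclude about its selection rule.

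**What to change.** In the Assessment schedule section, replace the reference to low-risk children having developed a disorder with a measured quantity: the proportion of low-risk children whose self-report RCADS at T4 is at or above the age-specific 80th-percentile cut-off already used for selection. Report parent-rated BIS impairment as supporting information.

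Set this proportion beside the same RCADS measure at T4 in the minimal-information arm, overall and by inclusion pathway. Pathway is already a randomisation stratum, so the split needs no new data.

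Add two statements of scope:
- Randomised children who were below the RCADS cut-off at T0 can only have entered through the HRI. A comparison restricted to children below the cut-off at T0 therefore tests only the HRI part of the rule, not the symptom part.
- The conclusion concerns elevated symptoms at 24 months, not incidence of disorder.

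Also state which cut-off applies to the oldest children. Those aged 17 at T0 will be 17 + 2 = 19 at T4, and the article does not list its age segments.

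The cost is wording, since Tables 1 and 2 already schedule the RCADS at T4 for both groups. The downside is a weaker claim than onset of disorder.
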